### Randomization and procedures to minimize bias

Following consent and the baseline (pre-randomization) assessment, a trial identification number is assigned to the participant. Eligible consenting participants are randomized to MST-PSB or MAU on a 1:1 basis by the Trials Unit at UCL through the use of a secure randomization service that ensures allocation concealment. A computer-generated adaptive minimization algorithm that incorporates a random element is used with the following stratification factors: gender, age (10–14, 15–17), conduct problems presenting with problem sexual behaviour (yes or no) and age differential between the perpetrator and victim (<4 years or ≥4 years). These strata were selected because previous research has shown that a greater age differential between perpetrator and victim, and whether the young person is also displaying antisocial behaviour, are associated with more severe maladjustment and poorer long-term outcomes [6, 47, 48].

To minimize the possibility that RAs will learn of the treatment allocation for any individual participant, the RAs are blind to treatment allocation at randomization, and there is no direct communication between RAs and therapists. This procedure has been used in the START trial of standard MST [28] and has proven to be effective.

### Planned interventions

#### Multisystemic Therapy for Problem Sexual Behaviour

MST is based on the premise that behaviour is multi-causal; therefore, to change an individual’s behaviour successfully, multiple drivers need to be addressed. Consequently, the approach works with the young person’s ecology (namely, the young person’s primary relationships, behaviour and the developmental challenges at home, school and in the community), as well as the young person themself; places a high premium on approaching each young person/family as unique; and has a specific focus on parental/carer involvement in treatment delivery, due to carer(s) being viewed as the key agents of change. MST has a track record of working with hard-to-reach, complex families with multiple needs. To increase engagement and formulation, a family is allocated one therapist who employs interventions that are strongly supported and informed by research. The sessions take place in the family home, and outreach work is undertaken when necessary. The family also has access to 24-hour/7 days a week telephone support with a therapist who is fully briefed on the family’s difficulties, safety plans and stage of therapy, so that support is readily available in times of crisis.

MST was originally developed to work with youth who engage in antisocial behaviour. In recent years, the research and implementation base of standard MST has been built upon to produce interventions to treat young people with a range of other difficulties, such as substance abuse, diabetes management, psychiatric care, child abuse and neglect, as well as problem sexual behaviour.

Problem sexual behaviour is an exclusion criterion for standard MST. MST-PSB, the adaptation of standard MST specifically for working with youths showing PSB, aims to reduce the level of both sexual and non-sexual offending in the target population. Supplementary to MST, MST-PSB has a greater focus on safety planning, individual factors (for example, impulsivity, social anxiety), and interventions specific to problem sexual behaviour, such as offence clarification sessions aimed at increasing accountability and safety and the promotion of normative sexual behaviour. Furthermore, family therapy techniques, such as structural and strategic family therapy interventions, are utilized to a greater extent than in standard MST, as well as peer interaction skills. In addition, where this is a factor, the impact of the young person’s own victimization and experience of abuse is assessed.

The intervention procedure consists of regular visits to the family home to meet with the young person and/or parent(s) for approximately 1 hour. Visits take place approximately three times per week at the beginning of the intervention and the frequency is reduced as the intervention progresses. Overall, the intervention time is 5 to 7 months.

In the STEPS-B trial, MST-PSB will be delivered by a team of at least three specially trained clinicians under the supervision of an MST supervisor, with weekly 1-hour conference calls for consultation with an MST Services staff member. It is expected that MST-PSB therapists will also have the support of consultation with local mental health professionals. To further support the therapists’ supervision and delivery of the intervention, a Therapist Adherence Measure-Revised (TAM-R) will be completed by the participants’ carers with an independent researcher every 3 weeks to review the therapist’s adherence to the nine principles of the MST model [49]. In addition, therapists will complete a Supervisor Adherence Measure bimonthly to rate the supervisor’s adherence to the nine principles.

The MST-PSB team at the Brandon Centre is centrally funded by the Department of Health and will have been operational for 18 months by the start of the clinical trial; during this period the intervention has been offered to referrers free of charge (otherwise, cost is approximately £10,000 per case). This bedding-in period has established the team in the referring boroughs, which has led to relationships being built with referring agencies and other intervention services addressing harmful sexual behaviour and to referrers increasing their awareness and knowledge of the referral criteria and intervention. Furthermore, as the MST-PSB team has been funded on condition that it participates in the research trial, greater collaboration is achieved between the MST-PSB team and research team by working together to meet joint targets such as recruitment numbers. Finally, the initial 18-month period will have given the MST-PSB team experience of implementing and addressing challenges to delivering the intervention in a UK context, therefore increasing treatment fidelity prior to the start of the transportability evaluation. To further ensure treatment fidelity, the MST developers have developed an extensive quality assurance system [50] and, in common with all MST sites, the Brandon Centre is licensed by MST Services (Charleston, SC, USA).

#### Management as usual

MAU constitutes the way in which a case would be managed if MST-PSB was not available. The authors aim to compare MST-PSB with specialist interventions for adolescents displaying problem sexual behaviour provided through social services, youth offending services and CAMHS. It is not assumed that MAU will be uniform across the referring boroughs. Instead, it is expected that the length, intensity and models of intervention will vary. Furthermore, it is envisaged that some young people assigned to MAU may not receive any interventions, owing to the limited service provision available where they live. The trial will map the specific profiles of services delivered to youth randomized to the MAU arm of the trial, as well as the approaches used within MST-PSB.

The service to which a young person may be referred for MAU is likely to depend on the severity of the case, the interventions available in the borough’s directorate and the provision for the borough to spot purchase. Potential options for MAU may include: AIM (Assessment Intervention and Moving on), an assessment and intervention programme that can be delivered by CAMHS, youth offending teams and social care practitioners; Youth In Need, a group CBT programme with an emphasis on the developmental perspectives underpinning offence-related issues; The Portman Clinic, which provides individual therapy using a psychoanalytical model; SWAAY Child and Adolescent Services Ltd or the Bracton Centre, both of which offer residential placements for young people where they can access a variety of individual and group programmes specifically targeting problem sexual behaviour as well as attending to the young person’s educational needs; and practitioners in CAMHS, social care and youth offending services who have developed expertise in working with this client group. Depending on the seriousness of the problem sexual behaviour, the young person may attend the NSPCC’s National Clinical Assessment and Treatment Service (the NSPCC is a UK children’s charity with a major focus on abuse prevention and intervention), which offers assessment, a multidisciplinary risk assessment report and treatment. The project’s intervention models include CBT, psychotherapy, individual psychological therapy and group therapy.

### Assessments and outcome measures

To maximize the clinical validity of the outcome evaluations, assessments are being made using multiple methods (for example, objective offending indices, semi-structured interviews, standardized questionnaires) completed by different informants (for example, the young person, carer(s) and teacher(s)) who are significant in the multiple domains that characterize young people’s functioning (home, school, community).

#### Feasibility outcomes

The feasibility outcomes measure chosen variables that the investigators hypothesize will be related to the effective implementation of MST-PSB in the United Kingdom.

First, it is predicted that specific characteristics of young people referred for displaying problematic sexual behaviour will be more likely to result in these young people being randomized into the trial. The specific characteristics that will be examined include the age of the young person, severity of the young person’s problematic sexual behaviour, source of the referral, and whether or not the young person was involved in judicial proceedings at the time of randomization.

Second, the beliefs and attitudes held by professionals working in the agencies and services that will refer into the trial will be evaluated. The data gathered concerning their beliefs and attitudes will include the degree to which they are supportive of a family-based intervention for a young person displaying problematic sexual behaviour; the degree to which they are in accord with the procedures and demands associated with an RCT research evaluation, including the randomization and its consequences; and the degree to which they view the institutions and agencies that manage young people showing problematic sexual behaviour as able to support an RCT evaluation.

The trial team has developed a bespoke 15-item questionnaire (the Feasibility Questionnaire) to assess beliefs and attitudes in the following areas: family treatment as an appropriate intervention for young people showing problematic sexual behaviour (for example, ‘My preference would be for 1:1 work to take place with a young person who displayed problematic sexual behaviour over a family approach’); support for RCT evaluations of young people showing problematic sexual behaviour (for example, ‘I have ethical concerns when referring a young person into a clinical trial where the young person is randomly assigned to an intensive treatment or a control group (which may involve a less intensive intervention)’); and perceptions of the systemic context (agencies and institutions) as facilitative of RCT evaluations (for example, ‘I am knowledgeable of different services that support young people who are perpetrators of problematic sexual behaviour (excluding MST-PSB)’). These three areas have been chosen on the basis of preliminary discussions with referrers and agencies that manage young people showing problematic sexual behaviour in the localities where recruitment will take place, as well as our previous experience liaising with referrers and the major agencies involved in providing CAMHS while conducting two earlier RCTs of standard MST, including a large multi-site trial [28]. The experience of implementing previous RCTs has been considered in light of the guidelines for strategic arrangements, assessment and planning, and interventions set out by the joint inspection of the effectiveness of multi-agency work with children and young people who have committed sexual offences in the United Kingdom [43]. The Feasibility Questionnaire will be completed by approximately 100 practitioners who are involved in the management and treatment of young people who show problematic sexual behaviour and who will potentially refer participants to the trial.

Third, the acceptability of the trial protocol to young people and their carers will be investigated through qualitative interviews following the completion of treatment. The qualitative interviews concerning participants’ experience and views of the trial protocol will be part of a larger semi-structured interview, which will include discussion of their experiences of the MST-PSB and MAU interventions (see ‘Interviews’ below). The part of the interview that elicits information regarding the trial protocol will focus on several domains: the process of identifying and discussing the young person’s problematic sexual behaviour as part of the family visit at which consent is obtained; the explanation of randomization and their understanding of the two treatment options available to them; and their perceptions regarding the appropriateness and challenges of completing the study’s standardized measures.

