The available data on prevalence and the difficulty gaining accurate estimates of incidence and service use suggest that the size of the pool of available participants to recruit into an RCT for problem sexual behaviour is uncertain. Therefore, the success of the trial is likely to depend on efficient identification of potential participants. It will also rely on established systems for providing specialist treatments for adolescent sexual offenders and for managing their mental health needs, given that judicial processes can determine the offenders’ availability for mental health interventions or delay timely provision of treatment. Two recent reviews of the provisions for juvenile sexual offenders in the United Kingdom noted that, despite examples of good practice, services for identifying and intervening with young people displaying problem sexual behaviour are underdeveloped [39]. For example, a recent examination of multi-agency responses to children and young people who sexually offend concluded that identification of young people’s problem sexual behaviour was often subject to disbelief, minimization and denial by professionals and by families; that much work was characterized by poor communication between the relevant agencies, with inadequate assessment and joint planning; and that cases were slow to get to court, on average taking 8 months between disclosure and sentencing, resulting in lengthy periods when little or no work was done with the young person [43]. The findings from this joint government inspection suggest that implementation of the MST-PSB trial will require substantial liaison and problem-solving with all relevant stakeholders to help identify young people who are appropriate for the trial and would benefit from the available interventions, as well as planning to accommodate judicial processes that will impact on the timely provision of both MST-PSB and MAU interventions.

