### Aims

The aim of STEPS-B is to carry out a feasibility trial that will inform policymakers, commissioners of services and professionals about the potential for implementing MST-PSB as a programme for intervening with young people showing problem sexual behaviour. Should MST-PSB show potential in the United Kingdom context, the trial will determine what would be necessary to implement the programme more fully and at a scale that would warrant a full trial.

The trial will investigate whether MST is associated with the elimination or reduction of levels of sexual and nonsexual offending; reduction or elimination of problem sexual behaviours; reduction in nonsexual antisocial behaviour; less time spent in custodial institutions; and improved educational outcomes. It will also aim to establish the cost of MST-PSB relative to MAU, and the cost-effectiveness of providing this intensive form of intervention against the background of costs incurred in the 20-month period following randomization.

Finally, the trial will investigate specific feasibility issues that pertain to effective implementation of MST-PSB in the United Kingdom. These include: specific characteristics of young people’s problem sexual behaviour, where they are referred from, and what services have been or are being provided to them whether or not they are randomized into the trial; the beliefs and attitudes held by professionals around family intervention for this population, given that the young person will remain in the family home despite having committed sexually harmful behaviour towards other young people, including, in some cases, a sibling living in the same home; the degree to which professionals are supportive of the procedures and demands associated with an RCT research evaluation, including the randomization and its consequences; and the degree to which the institutions and agencies that manage young people showing problem sexual behaviour, such as the courts and child protection services, are able to support an RCT evaluation. It will also investigate the acceptability of the trial protocol to young people and their carers, and will gather information on their experience of MST-PSB and MAU interventions, through qualitative interviews following completion of treatment.

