#### Screen 3 and consent

Unless the family expresses a decision not to participate at the time of the introductory visit, they are given a minimum of 3 days to consider whether they would like to join the clinical trial. If the RA does not hear from the family within the agreed time period, the RA telephones the family, answers any additional questions they may have, and arranges an appointment for a research assessment.

At the research assessment, each young person and primary carer(s) sign informed consent forms agreeing to join the clinical trial, including permission to access the police, correctional and educational databases, which remains in effect for 20 months. For families who sign the consent forms, the RA administers pre-randomization questionnaires and measures are completed during this contact (that is, before group assignment).

Once the young person and family’s eligibility have been confirmed and the instruments completed, the RA contacts the trial centre and relays the family’s randomization details. The clinical team informs the family and referrer of the outcome of randomization within 48 hours of the consent and pre-randomization visit being completed.

Once the family has completed the compulsory instruments to be able to join the trial, the young person is asked whether they would like to take part in the optional Child Attachment Interview (see Measures, below). If the young person and primary carer(s) agree, an additional meeting is arranged within 1 week of the date of randomization. At this additional visit, consent forms are signed by the primary carer(s) and young person and the Child Attachment Interview is conducted.

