### Secondary outcomes

The feasibility outcome evaluating individual and systemic factors associated with recruitment into the trial will be analysed using logistic regression. The total score and subscale scores on the Feasibility Questionnaire will undergo descriptive analyses to characterize the direction and range of attitudes by referrers involved in the MST-PSB trial. As noted above, qualitative interviews eliciting the views of young people and their carer(s) on the underlying principles and demands of participating in an RCT will be analysed using IPA.

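### Judicial involvement, a listed predictor of being randomized, is defined at the time of randomization, which referrals that are not randomized never reach

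*Protocol article*

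**What the plan says.** Under Feasibility outcomes, the protocol article predicts that certain characteristics of referred young people "will be more likely to result in these young people being randomized into the trial". It lists four: age, severity of the problematic sexual behaviour, source of referral, and "whether or not the young person was involved in judicial proceedings at the time of randomization". Only the last is tied to a time point.

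The statistical analysis plan within the article, under Secondary outcomes, gives the method: "The feasibility outcome evaluating individual and systemic factors associated with recruitment into the trial will be analysed using logistic regression".

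The Aims show that young people who are not randomized are meant to be covered. They include where the young people are referred from and "what services have been or are being provided to them whether or not they are randomized into the trial".

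The Exclusion criteria bar a case whose sexual offence is under police investigation when it is referred.

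**The concern.** The outcome of the regression is randomized yes or no among referrals. A predictor of that outcome needs a value in both groups, taken at a comparable point. Judicial involvement is defined at a moment that only the yes group reaches.

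The question matters to a feasibility trial. Under The current trial, the article says that judicial processes can decide young people's "availability for mental health interventions or delay timely provision of treatment", and it calls for planning around them. The judicial coefficient is the quantitative evidence on that barrier. If it cannot be estimated, or if it mixes legal status with the date on which status was taken, it gives poor guidance for designing a full trial.

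The police-investigation exclusion is a lesser, related matter. A case barred by that rule cannot be randomized. If such cases enter the model and some count as being in judicial proceedings, part of the coefficient reflects the eligibility rule and not how recruitment works.

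**Working it through.** The plan states no figure for this analysis, so there is none to reproduce. The check is mainly logical.

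**Does the predictor exist in both outcome groups?**

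- Outcome: randomized or not, among those referred (Feasibility outcomes).
- Predictor: judicial proceedings, yes or no, at randomization (same section).
- Randomized referrals have a randomization date, so the predictor is defined.
- Non-randomized referrals have no randomization date. Feasibility outcomes, Aims, the recruitment sections and the analysis section give no alternative, so the predictor is undefined.

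Write the 2×2 table as *a*, *b* for randomized referrals with and without judicial involvement, and *c*, *d* for non-randomized. Read literally, *c* = *d* = 0 among cases with a value, and OR = *ad*/(*bc*) = 0/0. As a numerical check, a logistic model was fitted with the planned 80 randomized and an assumed 80 not randomized, the predictor being present only for the former. All 80 complete cases had outcome 1, and the fit gave perfect-separation warnings and did not converge. Imputation would not help, because no non-randomized referral supplies an observed value to learn from.

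**Would an ad hoc substitute date do?** Randomization comes after a telephone consultation, the referral form, an introductory home visit, up to three sessions where a carer denies the behaviour, at least 3 days' consideration unless the family declines at the visit, and the baseline assessment (Screens 1 to 3). A referral that drops out does so at some earlier step. The article also cites an average of 8 months between disclosure and sentencing, so legal status can change along this pathway. Status taken at exit for one group and at randomization for the other would be observed at systematically different stages.

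**Could the gap be filled later from records?** Consent forms, signed at the research assessment, give "permission to access the police, correctional and educational databases". Families who leave before then have not given it, so prospective recording is the safer route.

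**How could the exclusion rule matter?** This is an illustration on assumed inputs, none of them from the article. Let *f* be the share of referrals excluded for police investigation, *g* the share of those coded as in judicial proceedings, *j* the judicial share among the rest, and *r* the share of the rest randomized, with a true OR of 1 among the rest. As shares of all referrals:

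- *a* = (1−*f*)*jr*
- *b* = (1−*f*)(1−*j*)*r*
- *c* = (1−*f*)*j*(1−*r*) + *fg*
- *d* = (1−*f*)(1−*j*)(1−*r*) + *f*(1−*g*)

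Take *r* = 0.5, *j* = 0.2 or 0.4, and *f* = 0.1, 0.2 or 0.3. The apparent OR is:

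- *g* = 1: 0.19 to 0.64. For example, *j* = 0.2 and *f* = 0.3 give 0.07 × 0.28/(0.28 × 0.37) = 0.19.
- *g* = 0.5: 0.49 to 0.93.
- *g* = 0: 1.28 to 2.43. For example, *j* = 0.4 and *f* = 0.3 give 0.14 × 0.51/(0.21 × 0.14) = 2.43.

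When *g* = *j* there is no distortion. With the excluded cases removed (*f* = 0), the OR is 1. So size and direction both depend on an overlap that the article does not give.

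**The case against.** The strongest reply is that the phrase should be read sensibly, as status around the recruitment decision. The Aims show that data on non-randomized referrals are intended, and the recruitment procedure has three eligibility decisions at which status could be noted. Nothing says it will go unrecorded. The denominator and coding of one covariate are also details that an article may leave to the full protocol or analysis plan.

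Part of this stands. A reader might infer that the data will in fact be missing for every non-randomized referral. The article does not say so; that result follows only if the phrase is applied as written. The unstated denominator is not a fault in itself. But the time point is not an omitted detail. It is stated, and it does not fit the stated outcome. The sensible reading appears nowhere in the text and still leaves timing that differs by outcome.

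A reader might also infer that the exclusion criterion already fixes much of the judicial coefficient. The documents do not support that. Police investigation at referral and judicial proceedings are different legal stages. Cases are screened by telephone against the criteria before a form is submitted, so barred cases may never enter the set analysed. The odds ratios above rest on assumed shares.

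It is fair, too, that status at the recruitment decision may describe the barrier better than status at referral.

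**Conclusion.** The definition is wrong as written. Judicial involvement is tied to an event that only one outcome group reaches, so its coefficient cannot be estimated if the text is followed literally. With improvised dates, its timing would differ by outcome. This conclusion rests on the text alone and needs no assumed figure.

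The scope is narrow: one of four listed predictors in one feasibility analysis. Age, severity and referral source carry no such time point, and no timing fault is shown for them. Randomization, the primary outcome and the treatment comparison are untouched.

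The exclusion rule supports a precaution, not a finding of bias. Its overlap with judicial proceedings is unknown, and it drops out if only otherwise eligible referrals are modelled. The change is worth making because it is cheap and concerns a barrier to recruitment that the article itself singles out.

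**What to change.** Under Feasibility outcomes, replace the time point with one common to all referrals, such as first referral contact (telephone consultation or referral form). Record judicial involvement then, prospectively, for every referral whether or not randomized. The article does not say that the referral form captures this, and a case stopped at the telephone stage may have no form, so the item should be available at either step.

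In the analysis section, report exclusions for police investigation descriptively, and fit the logistic model for randomization among otherwise eligible referrals.

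The cost is two short text changes and one item at first contact. The eligible-only model has fewer cases, and status at referral may differ from status at the recruitment decision; that limitation should be stated when the result is reported. As the article describes recruitment as ongoing in the trial's third year, referrals already closed may lack the item, and their number should be given.
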